## 6.2 SECONDARY ENDPOINTS

The secondary endpoints are:

- Average cost of caring for a patient for each of the two strategies
- Sensitivity, specificity, error rates, positive and negative likelihood ratios of FCH PET/CT and MIBI SPECT/CT
- Rate of minimally invasive surgeries and bilateral cervical explorations for each diagnostic strategy
- Number of failures of parathyroid surgery (regardless of the type of surgery performed), defined by the persistence of primary hyperparathyroidism 6 months after surgery
- Complications occurring within one month of surgery: infections, hematomas, laryngeal recurrent nerve injury
- Cohen's kappa coefficients between the 2 independent readers, during their first reading, then during their second reading (3 months later); as well as between the first and second reading of each of the 2 readers
- Serum PTH concentration at baseline
- To compare detection sensitivities of FCH PET-CT at 10 min and 60 min post-injection, as well as semi-quantitative analysis.
- Scores for the 6 dimensions (comfort, attention, information, pain management, waiting times, intimacy) of the EVAN-G questionnaire administered perioperatively (4 to 48 hours after the intervention before discharge from hospitalization)

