| Adverse events                                                                                                        |                          |  |     |        |
| Patient satisfaction (EVAN-G questionnaire)                                                                           |                          |                          |  ** |                                |

113  
114 \* Biochemistry: Calcium, phosphoremia, albumin, creatinine, PTH, 25 OH vitamin D

115 \*\*completed within 4 to 48 hours after surgery, before discharge from hospitalization

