### 5.2 SECONDARY OBJECTIVES

The secondary objectives are to:

- Conduct a medico-economic evaluation comparing the costs and effectiveness of the two diagnostic strategies
- Estimate the diagnostic performance of each strategy
- Assess the number of failures at 6 months of parathyroid surgery (regardless of the type of surgery performed) for each strategy
- Assess post-surgical complications
- Assess intra- and inter-observer variability for the interpretation of FCH PET/CT and MIBI SPECT/CT
- Explore the relationship between the positivity of imaging tests, including FCH PET/CT, and serum PTH concentration at baseline
- Evaluate the detection performance of FCH PET-CT on an early imaging time point at 10 min post-injection compared to that of acquisition at 60 min.
- Assess patient satisfaction in the perioperative period

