### 7.2 STUDY DURATION

The expected duration of the recruitment is 30 months.

The duration of the follow-up period is 6 months post-surgery.

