#### ❖ **Follow-up at 1 and 6 months after surgery**

**A laboratory assessment** including calcemia and PTH will be performed at 1 and 6 months after surgery.

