## 9 MEDICO-ECONOMIC STUDY

The medico-economic analysis will be carried out from the point of view of health insurance. From this perspective, only direct hospital costs will be included in the analysis. They will include the costs of diagnosis, the costs of surgery (type of surgical procedure, duration of intervention and hospitalization, anesthesia) and the cost of possible complications (hematomas, infections, damage to the recurrent laryngeal nerve, chronic hypoparathyroidism).

The efficacy endpoint will be the cure rate at one month (normalization of serum calcium at one month post-surgery). An incremental cost-effectiveness ratio will be estimated to establish the average cost needed to cure an additional person by moving from the usual strategy to the new strategy.

A sensitivity analysis of the uncertain parameters of the model will be performed to test the robustness of the cost-effectiveness ratio.

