### 10.3 INVESTIGATOR’S RESPONSIBILITIES

#### 10.3.1 Detection and registration of adverse events

All adverse events have to be searched, reported and recorded, processed and evaluated.

All adverse events occurring, once the informed consent form has been signed, **during treatment and 30 days after the last study drug administration**, must be recorded by the investigator.

The intensity of the events will be estimated according to the NCI-CTCAE version 5.0 classification (grade 1 to 5 toxicity). The intensity of adverse events not listed in this classification will be graded as follows:

- **Grade 1: mild** : Discomfort noticed but no disruption of normal daily activity
- **Grade 2: moderate** : Discomfort sufficient to reduce or affect daily activity; no treatment or medical intervention is indicated although this could improve the overall well-being or symptoms of the patient
- **Grade 3: severe** : Inability to work or perform normal daily activity; treatment or medical intervention is indicated in order to improve the overall well-being or symptoms; delaying the onset of treatment is not putting the survival of the patient at direct risk
- **Grade 4: Life-threatening/disabling** : An immediate threat to life or leading to a permanent mental or physical conditions that prevents work or performing normal daily activities; treatment or medical intervention is required in order to maintain survival
- **Grade 5: Death AE or resulting in death**

The investigator will specify for each event:

- ✓ The seriousness
- ✓ The date of start +/- the date of end of the event
- ✓ The duration
- ✓ The intensity
- ✓ The causality assessment
- ✓ The outcome

If a SAE occurs, the sponsor should be notified of the event awareness by the investigator without any delay. This will be done by mailing sponsor's Serious Adverse Event Report Form.

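### The complications endpoint leaves out chronic hypoparathyroidism, which section 9 costs as a surgical complication, and no other endpoint captures it

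*Protocol*

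**What the plan says.** The secondary objective in protocol section 5.2 is broad: "Assess post-surgical complications", with no limit of type or time. The endpoint that serves it is closed. Section 6.2, and the synopsis in identical terms, give "Complications occurring within one month of surgery: infections, hematomas, laryngeal recurrent nerve injury".

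Section 9 sets out the hospital costs for the cost-effectiveness analysis. These include "the cost of possible complications (hematomas, infections, damage to the recurrent laryngeal nerve, chronic hypoparathyroidism". The first three items match section 6.2; the fourth does not appear there. Section 9 is the only place in the protocol where hypoparathyroidism is named, and it comes with no definition, threshold or time point.

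The data that bear on it are largely planned. Section 7.4.3 has a laboratory assessment "including calcemia and PTH will be performed at 1 and 6 months after surgery". The flow chart ticks blood tests at the same two visits, with the panel "Biochemistry: Calcium, phosphoremia, albumin, creatinine, PTH, 25 OH vitamin D". Section 7.2 adds: "The duration of the follow-up period is 6 months post-surgery".

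**The concern.** A chronic state cannot be established inside a one-month window, and the item is not on the list in any case. Section 6.2, followed as written, can never report a case of a complication that section 9 treats as a consequence of the surgery.

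The omission touches the trial's argument. Section 4.1 says minimally invasive surgery brings fewer complications than bilateral exploration. Sections 4.2 and 4.3 expect the higher price of PET to be offset partly through complications. When both scans are negative, section 7.4.4 has all four parathyroid sites explored. A harm to parathyroid function is therefore directly relevant to the comparison being argued. If the economic report counts it and the clinical report does not, the two will describe different safety outcomes for the same patients.

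**Working it through.** The plan gives no figure on this point, so the check sets the sections side by side.

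**1. The two lists.**

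| Complication | 6.2 and synopsis (within one month) | Section 9 (costed) |
|---|---|---|
| Infection | yes | yes |
| Hematoma | yes | yes |
| Recurrent laryngeal nerve injury | yes | yes |
| Chronic hypoparathyroidism | no | yes |

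One of the four costed items has no place in the endpoint. The synopsis repeats section 6.2, so this is not a slip in one section.

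**2. Does another endpoint capture it?**

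- *Surgical failure at 6 months (6.2)* is defined by persistent primary hyperparathyroidism. Low calcium with low PTH is the opposite disturbance and is not a failure on that definition.
- *Cure in the primary endpoint.* Section 6.1 uses serum calcium at one month only. The synopsis uses calcium and PTH at one and six months. A low value might fail either version as not normalised, but the patient would then be grouped with every other uncured patient. Nothing would label the result a complication.

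**3. Does adverse event recording fill the gap?** The flow chart ticks adverse events at 1 and 6 months after surgery, and section 10.2.1 counts an abnormal laboratory finding as a possible adverse event. Section 10.3.1, however, limits recording to "during treatment and 30 days after the last study drug administration". The study drugs in section 8 are the two imaging tracers. Section 7.4.3 allows surgery up to 12 weeks after the last scan:

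- 12 weeks = 12 × 7 = 84 days
- 84 − 30 = 54 days

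On that rule, recording can end up to 54 days before the operation. Because surgery follows imaging, the 6-month visit always falls outside it. Section 10.3.2 keeps late serious events reportable, but only if they are serious and judged related to the study treatment or procedure. This route is not dependable.

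**4. Are the data there?** Calcium and PTH at 6 months are scheduled (flow chart, section 7.4.3). There are two weak spots. The histopathology paragraph of section 7.4.4 speaks of a visit between 1 and 6 months with serum calcium only. Concomitant treatments are mentioned only at inclusion (section 7.4.3), so supplementation at follow-up has no stated place.

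**5. What could be reported?** Section 11.1 plans 25 evaluable patients per arm and 58 included, or 58 / 2 = 29 per arm. With no case among n patients, the one-sided 95% upper limit for the risk is 1 − 0.05^(1/n):

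- n = 25: 1 − 0.05^(1/25) = 11.3%
- n = 29: 1 − 0.05^(1/29) = 9.8%

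The item can be described by arm but not usefully compared.

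**The case against.** The best reply is that a cost input need not be an endpoint. Section 9 also costs operating time, hospital stay and anesthesia, none of which is an endpoint in section 6.2. No section says that the economic analysis takes its complication counts from section 6.2. A reader might infer that the cost analysis would hold no case of chronic hypoparathyroidism; the documents do not support that, because section 9 could count cases directly from the 6-month laboratory results. This part of the reply stands. It does not remove the mismatch: the complications objective would still be answered without a harm that the protocol names.

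A second reply is that low calcium or PTH at 6 months could be recorded as an adverse event. It stands only in part, because the flow chart and section 10.3.1 disagree and section 10.3.1 would exclude that visit.

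A third is that definitions are commonly left to the SAP, which is not shown. That is fair for the operational definition. The content and window of the endpoint are a different matter, since the protocol fixes both explicitly in two places.

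**Conclusion.** The inconsistency is real and worth correcting, at the level of a secondary endpoint. One of four complications costed in section 9 is missing from the complications endpoint, and nothing else in the protocol reliably captures it. The primary endpoint, its analysis and the sample size are untouched. The conclusion assumes only that the sections are applied as written and that the last study drug means the last tracer injection.

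Three further inferences go beyond the text:

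- A reader might want to state how many cases would be missed, or that they would materially change the complication total. The documents give no incidence and no expected total, so neither can be claimed.
- A reader might conclude that patients with low calcium are counted as normalised. No section says so, and on a plain reading a low value is not normal.
- A reader might suppose that the scheduled laboratory values settle the matter. They may not, since a patient on supplementation could show a normal calcium.

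The one-month window is not itself an error for infection and hematoma. The fault lies in the mismatch with section 9 and with the unrestricted objective in section 5.2.

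**What to change.** Put section 6.2, the synopsis and section 9 on one list of complications with stated time points:

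- Add chronic hypoparathyroidism to the complications endpoint, assessed at 6 months from the calcium and PTH already scheduled.
- Use a definition that the sponsor prespecifies and that says how supplementation at follow-up is taken into account.
- Keep the one-month window for infection and hematoma.
- Use the same count in section 9 and report it descriptively by arm.
- Reconcile the adverse event window in section 10.3.1 with the flow chart, and the looser follow-up wording in section 7.4.4 with section 7.4.3, so that 6-month PTH is secured for every patient.

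No new visit, blood sample or patient is needed, and the sample size does not change. The cost is amended wording, one more descriptive item, possibly one case report form field for supplementation, and a reported complication rate that may be slightly higher.

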## 7 STUDY DESIGN

### 7.1 METHODOLOGY

We propose a phase III, randomized, open-label, multicenter study comparing, between each diagnostic strategy, the proportion of patients for whom the first-line imaging technique (MIBI SPECT/CT or FCH PET/CT) was used to guide the surgical procedure wisely (true positive minimally invasive surgery decision and patient cure).

### 7.2 STUDY DURATION

The expected duration of the recruitment is 30 months.

The duration of the follow-up period is 6 months post-surgery.

### 7.3 SUBJECTS SELECTION

#### 7.3.1 Inclusion criteria

- Patient over 18 years of age
- Patient with primary hyperparathyroidism and for whom excision surgery is planned
- Laboratory assessment confirming the diagnosis of primary hyperparathyroidism (elevated serum PTH and calcium concentrations)
- For women of childbearing potential, negative pregnancy test at baseline
- Affiliation to a social security scheme
- Patient who has signed written consent

#### 7.3.2 Non inclusion criteria

- Patient deprived of liberty, under guardianship or curatorship
- Hypersensitivity to TECNESCAN SESTAMIBI

- 249 - Any associated medical or psychological condition that could compromise the patient's
- 250 ability to participate in the study
- 251 - Pregnant or breastfeeding woman
- 252 - History of parathyroid surgery
- 253 - Patient with MEN1
- 254 - Known hypersensitivity to Fluorocholine or any of the excipients (sodium chloride, water for
- 255 injections)

## 256 **7.4 STUDY PLAN**

### 257 **7.4.1 Consent sign**

258 The study will be proposed by the investigators to patients who meet the eligibility criteria. They will  
259 be given an information note and an informed consent form. Patients will have a reflection period  
260 before choosing to participate.

261 After obtaining the patient's consent by signing the study consent, the selection criteria will be  
262 checked prior to inclusion in the trial.

263 Study-specific examinations requested prior to inclusion (inclusion assessment) will be performed  
264 after signing consent and prior to randomization.

### 265 **7.4.2 Randomization procedure**

266 After obtaining the patient's consent by signing the study consent, verifying the selection criteria  
267 and carrying out the inclusion assessment, randomization will be carried out.

268 Randomization will be performed on software dedicated to the study via a web portal.

269 Eligible patients will be randomized to one of two strategies:

- 270 •Standard arm: MIBI SPECT/CT and then, if negative, FCH PET/CT scan.
- 271 •Experimental arm: FCH PET/CT scan, and then, in case of negativity, a MIBI SPECT/CT.

272 An identification number will be assigned to the patient and will be used throughout the study.

### 273 **7.4.3 Study conduct**

#### 274 ❖ **Inclusion Assessments**

275 Patients who are eligible for the trial and who have signed their consent to participate will be  
276 required to undergo a clinical examination and laboratory assessment prior to randomization as  
277 follows:

278 Relevant history (risk factors, associated pathologies, medical history and concomitant treatments)  
279 as well as the history of the disease and current treatments should be reported.

280 The physical examination should include weight and height.

281 A pre-therapeutic laboratory assessment should be carried out and will include: calcemia,  
282 phosphoremia, albumin, creatinine, PTH, 25 OH vitamin D.

283 Neck ultrasound.

284 These examinations correspond to those usually performed as part of the patient's routine  
285 management, in addition to MIBI SPECT/CT.

286 As part of the protocol, women of childbearing potential will be asked to take a urine or biological  
287 pregnancy test within 8 days prior to imaging.

288

#### 289 ❖ **Protocol Imaging Assessment**

290 FCH PET-CT and/or MIBI SPECT/CT will be performed within 12 weeks prior to parathyroid  
291 surgery. The 2 exams will be at least 48 hours apart.

For women who have undergone a PET exam with Fluorochol®, they will be contacted by telephone the day after the examination: this protocol precaution is put in place to ensure the absence of adverse effects, in accordance with the rapid biokinetics and elimination of Fluorochol® (approximately 12 hours).

Before performing these two examinations, the patient will be asked to fast for at least 4 hours before the injection without restriction of fluid intake.

The doctor will also check that the patient is not taking any contraindicated treatments with the imaging tests.

#### ❖ **Parathyroid Surgery**

It will be performed no later than 12 weeks after the last scintigraphic examination (MIBI SPECT/CT or FCH PET/CT).

Depending on the results of the imaging tests, the surgical procedure will consist of minimally invasive surgery or bilateral cervical exploration. The sample will be sent for extemporaneous examination during surgery.

A nasofibrosopic check-up will be performed postoperatively before discharge from hospitalization to assess the mobility of the vocal cords.

Patient satisfaction in the perioperative period will be assessed using the EVAN-G questionnaire within 48 hours of the procedure.

#### ❖ **Follow-up at 1 and 6 months after surgery**

**A laboratory assessment** including calcemia and PTH will be performed at 1 and 6 months after surgery.

### **7.4.4 Methods and Techniques Used or Evaluated in the Study**

#### ❖ **Imaging**

##### → **MIBI SPECT/CT**

The patient will receive 740 MBq of MIBI intravenously. Ten minutes post-injection, an early planar image of the thyroid compartment will be performed. Ninety minutes post-injection, a SPECT scan centered on the neck and mediastinum as well as a low-dose CT scan will be acquired. The lenses will not be included in the acquisition field: the scanner will start under the eye sockets. The duration of early acquisition will be 10 minutes and 25 minutes for SPECT/CT.

##### → **FCH PET/CT**

The patient will receive 1.5 MBq/kg FCH as an intravenous infusion in an injection box. Ten and sixty minutes post-injection, PET images centered on the neck and upper mediastinum as well as a low-dose CT scan will be acquired (total acquisition time of 10 minutes, corresponding to 2 steps of 5 minutes each). The lenses will not be included in the acquisition field: the scanner will start under the eye sockets.

The interpretation of PET/CT and SPECT/CT examinations will consist of indicating the presence of focal points suggestive of PTA by specifying its location, its CT scan dimensions, its volume, and for the PET, the metabolic profile.

For the same patient, each of the 2 examinations will be interpreted by 2 different operators in a blinded fashion. In case of a match, the result will be sent to the surgeon. In the event of a discrepancy, the examinations will be reviewed in a Multidisciplinary Consultation Meeting (RCP), and the result of the review of the examination will be communicated to the surgeon.

#### ❖ **Surgical decision for each diagnostic strategy**

In case of positive results of the first and/or second exam, the surgery will consist of a minimally invasive procedure, on an outpatient basis.

In case of negative imaging results (MIBI and FCH), an exploration of the 4 parathyroid sites will be performed.

In the case of multiple or ectopic PTAs, the surgical procedure will be adapted.

#### ❖ **Histopathological examination of surgical specimens**

Histopathological examination of the surgical specimens will confirm the presence or absence of PTA.

The results of the imaging assessment will be compared with the surgical and pathological results.

Patients will be seen again between 1 and 6 months post-surgery with a blood test to assess normalization of serum calcium.

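### In scan-positive patients, sensitivity is verified only in the surgical field the scan selected, so lesions left behind have no stated route to a false negative although calcium and PTH are collected

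*Protocol*

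**What the plan says.** Section 6.2 makes diagnostic performance a secondary endpoint: "Sensitivity, specificity, error rates, positive and negative likelihood ratios of FCH PET/CT and MIBI SPECT/CT". Section 11.2 plans to assess these measures for both tracers.

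Section 7.4.4 gives the yardstick. On histology: "Histopathological examination of the surgical specimens will confirm the presence or absence of PTA". On imaging: "The results of the imaging assessment will be compared with the surgical and pathological results". The next sentence mentions the postoperative blood test, but only as a check on normalization of calcium.

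The extent of surgery, and so of verification, follows from the scans (7.4.4):
- Positive: "In case of positive results of the first and/or second exam, the surgery will consist of a minimally invasive procedure, on an outpatient basis".
- Both negative: "In case of negative imaging results (MIBI and FCH), an exploration of the 4 parathyroid sites will be performed".
- Several or ectopic lesions: "In the case of multiple or ectopic PTAs, the surgical procedure will be adapted", with no further detail.

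Under 7.4.2 a negative first scan leads to the other tracer in both arms: "Standard arm: MIBI SPECT/CT and then, if negative, FCH PET/CT scan" and "Experimental arm: FCH PET/CT scan, and then, in case of negativity, a MIBI SPECT/CT".

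Section 7.4.3 schedules calcium and PTH at 1 and 6 months after surgery. The protocol uses postoperative biochemistry for the cure component of the primary endpoint (6.1), for surgical failure at 6 months (6.2) and for cost-effectiveness (section 9). It does not use it for sensitivity or specificity.

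**The concern.** A positive scan helps to choose the field in which it is then checked. Glands outside that field are not routinely explored or sampled. This is partial verification: how thoroughly a patient is examined depends on the test result.

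Every patient enters with laboratory-confirmed primary hyperparathyroidism (7.3.1), so each is expected to have at least one abnormal gland. If disease persists after scan-guided surgery, abnormal tissue was left behind. Two situations then have no stated place among the false negatives:

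1. The scan shows one of two adenomas, that one is removed, and the other remains.
2. The scan points to a site that holds no adenoma, and the true gland is not found at operation. The patient is a false positive at that site but need not enter TP/(TP+FN).

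Leaving such cases out of the denominator can only raise sensitivity. At stake is the credibility of the secondary accuracy estimates, which readers will compare between tracers.

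**Working it through.** **Plan's own figure.** The protocol states no number that depends on the reference standard. Its sample size (60% against 90%, one-sided 5%, 80% power) reproduces at 25 per arm, with power 80.4%, and is not affected by this point.

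**Which misses the stated reference can reveal**

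| Scan result | Verification under 7.4.4 | Is a miss visible? |
|---|---|---|
| Both scans negative | All four sites explored | Yes, for both scans |
| First negative, second positive | Surgery guided by the second scan | Yes, for the first scan if an adenoma is removed |
| Positive, wrong site | Guided field, with intraoperative examination (7.4.3) | Perhaps; no counting rule, and not if the gland is not found |
| Positive, second adenoma not shown | Guided field | Not if the second gland lies outside it |

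The gap is confined to the last two rows.

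**Patient-level illustration.** Inputs: c = proportion with a correct positive scan, taken as 0.90 for FCH and 0.60 for MIBI to match section 11.1; m = proportion with a positive scan at a wrong site that is not counted as a miss. The protocol gives no m, so the values below are assumptions. Each patient has one adenoma and negative scans are verified.

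- Mislocated scans counted as misses: sensitivity = c.
- Mislocated scans counted only as false positives: sensitivity = c/(1 − m).
- Overstatement = c/(1 − m) − c = c·m/(1 − m).

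| Tracer | c | m (assumed) | Apparent sensitivity | Overstatement (points) |
|---|---|---|---|---|
| FCH | 90% | 2% | 0.90/0.98 = 91.8% | 1.8 |
| FCH | 90% | 5% | 0.90/0.95 = 94.7% | 4.7 |
| FCH | 90% | 8% | 0.90/0.92 = 97.8% | 7.8 |
| MIBI | 60% | 5% | 0.60/0.95 = 63.2% | 3.2 |
| MIBI | 60% | 10% | 0.60/0.90 = 66.7% | 6.7 |

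In an arm of 25 with 22 correct, 1 wrong-site and 2 negative scans, the choice is between 22/24 = 92% and 22/25 = 88%.

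**Lesion-level illustration.** Let s be the observed sensitivity and m2 the assumed share of correctly scan-positive patients who have an unseen second gland. Per 100 patients there are 100s detected lesions, 100(1 − s) counted misses and 100·m2·s uncounted misses, so corrected sensitivity = s/(1 + m2·s).

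- s = 90%: 90/104.5 = 86.1% at m2 = 5%; 90/118 = 76.3% at m2 = 20%.
- s = 60%: 60/103 = 58.3% at m2 = 5%; 60/112 = 53.6% at m2 = 20%.

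**Direction between tracers.** At an equal m of 5%, FCH gains more (4.7 against 3.2 points). With m = 2% for FCH and 10% for MIBI, MIBI gains more (6.7 against 1.8). Without mislocation rates the sign of the difference cannot be fixed.

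**The case against.** The best defence is that the protocol sets no rule for true positives, false positives or false negatives and no unit of analysis, and that such detail commonly sits in an SAP, which is not shown here. Surgical results are also broader than histology. Readers record the location of each focus, and intraoperative examination may expose an empty site. Persistent disease is reported anyway, through the primary endpoint and the 6-month failure endpoint.

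Part of this stands. The absence of a detailed counting rule would not be a finding on its own. But the protocol does state a reference standard, and that standard leaves out the biochemical outcome. An SAP that followed it would inherit the gap.

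Three stronger readings might be inferred and are not supported:

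- **That missed lesions are never counted.** Patients negative on both scans have all four sites explored, and a negative scan followed by a positive one exposes the first scan's miss.
- **That the bias favours FCH PET/CT because fewer of its patients have four sites explored.** That exploration requires both scans to be negative in either arm. Under randomisation its expected share is the same if readings do not depend on scan order, and the bias otherwise turns on unknown mislocation rates.
- **That the primary result is affected to the same degree.** It requires cure as well as a true-positive decision, so most patients with tissue left behind already fail it.

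A further caution concerns the remedy. Persistence can follow incomplete removal at a correctly imaged site, and charging that to the scan would bias sensitivity downward.

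**Conclusion.** The point holds for scan-positive patients and for the secondary accuracy endpoints. The stated reference verifies the field the scan selected and omits biochemical data that the trial already collects, so sensitivity can be overstated for either tracer.

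The direction within each tracer is clear; the size is not. On the assumed shares above, the overstatement is about 2 to 8 points for FCH and 3 to 7 for MIBI at patient level, and about 2 to 14 points across the two tracers at lesion level. These figures show scale and are not estimates. Which tracer benefits more is unknown. The sample size and the primary comparison need no change on this account.

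**What to change.** In 7.4.4 and 11.2:

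1. Define the reference for diagnostic performance as surgery and histology together with calcium and PTH at 6 months.
2. State the unit of analysis, reporting both patient level and lesion level.
3. At patient level, count a positive scan whose site holds no adenoma as a miss in the sensitivity denominator, and also record it as a false-positive focus.
4. Count persistent hyperparathyroidism after scan-guided surgery as at least one missed lesion for that scan, unless surgical and pathology records attribute it to incomplete removal at a correctly imaged site.
5. Add a sensitivity analysis that uses surgery and histology alone.

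The cost is wording. No visit, test or procedure is added and clinical management is untouched. The reported sensitivities may be slightly lower, and some persistent cases will need adjudication from existing records.
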